### Trial sample size

The primary outcomes of this trial include changes in pain (NRS) and physical function (WOMAC) over 6 months and the intervention will be considered beneficial if it changes either one or both of the primary outcomes. A Cochrane Review shows that exercise has a moderate effect size for pain and function in knee OA [10]. Calculations thus assume an effect size between the least-performing treatment group (presumed to be the *Exercise* group) and the control group of 0.4. Given that the effect size between two treatments will be less than between treatment and control, we assumed an effect size of 0.3 between the *Exercise* group and the *Exercise plus weight management* group. We chose 0.3 because any smaller effect is unlikely to be clinically relevant or cost-effective to implement in real-world settings given the considerable expense of the weight management program relative to the exercise components of this combined intervention. Calculations also assume a correlation between baseline and follow-up measurements of 0.4, power 80, 15% loss to follow-up (based on our previous research [71, 72]), and two-sided significance level of 0.05. Based on these calculations we require 173 participants in each treatment group, and 69 participants in the control group arm, giving a total sample size of 415 participants.

There are different levels of clustering for each of the three groups; in the *Exercise* group, participants are clustered by physiotherapist, in the *Exercise plus weight management* group, people are clustered by physiotherapist and dietitian, and in the control group, there is no clustering. Given the geographical and demographic spread of participants, we expect that the intra-cluster correlation of outcomes treated by the same dietitian or physiotherapist to be of the order of 0.01. Modifying the formulae [73] to allow for correlations between baseline and follow-up measurements, and assuming that there are five dietitians delivering the *Exercise plus weight management* treatment, the effect size that can be detected between the *Exercise* and the *Exercise plus weight management* groups with 80% power given the originally calculated sample size increases slightly to 0.32.

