**Methods:**

Three-arm, pragmatic parallel-design randomised controlled trial involving 415 people aged ≥45 and ≤ 80 years, with body mass index ≥28 kg/m^2^ and < 41 kg/m^2^ and painful knee osteoarthritis. Recruitment is Australia-wide amongst Medibank private health insurance members. All three groups receive access to a bespoke website containing information about osteoarthritis and self-management. Participants in the *Exercise* group also receive six consultations with a physiotherapist via videoconferencing over 6 months, including prescription of a strengthening exercise and physical activity program, advice about management, and additional educational resources. The *Exercise plus weight management* group receive six consultations with a dietitian via videoconferencing over 6 months, which include a very low calorie ketogenic diet with meal replacements and resources to support behaviour change, in addition to the interventions of the *Exercise* group. Outcomes are measured at baseline, 6 and 12 months. Primary outcomes are self-reported knee pain and physical function at 6 months. Secondary outcomes include weight, physical activity levels, quality of life, global rating of change, satisfaction with care, knee surgery and/or appointments with an orthopaedic surgeon, and willingness to undergo surgery. Additional measures include adherence, adverse events, self-efficacy, and perceived usefulness of intervention components. Cost-effectiveness of each intervention will also be assessed.

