For many people with OA, undertaking an exercise and/or weight management program requires considerable changes in lifestyle behaviours over prolonged periods of time. As such, it is important that intervention development is underpinned by behaviour change theory, and informed by best practice in chronic disease management and self-management support programs. Interventions must include provision of high quality information. However, education alone is insufficient to support behavioural change. Healthcare clinicians must also have the communication and psychosocial skills necessary to facilitate long-term changes in behaviour [32, 33]. Incorporating behavioural counselling [34, 35] and specific behaviour change techniques that are effective for supporting change in exercise and eating behaviours in this population [36] into intervention design will facilitate participants to achieve and sustain effective self-management practices in the long-term.

The aim of this study, conducted in a private health insurance setting, is to compare the effectiveness of two remotely-delivered, evidence- and theory-informed, behaviour change interventions to provide information and behaviour change support for i) exercise and; ii) exercise plus weight management, to each other, and to an information-only control for people with knee OA who are overweight or obese. We hypothesise that the exercise plus weight management intervention will lead to greater improvements in pain and function than the exercise intervention and that both interventions will be more effective than information only.

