### Primary outcomes

Primary outcomes are overall average knee pain severity in the last week measured on an 11-point numeric rating scale (NRS), where 0 = ‘no pain’ and 10 = ‘worst pain possible’ [58], and physical function assessed using the physical function subscale of the Western Ontario and McMaster Universities (WOMAC) Osteoarthritis Index [59]. The WOMAC is a disease-specific self-report instrument which has demonstrated validity, reliability, and responsiveness [60]. The physical function subscale contains 17 questions scored from 0 to 4, giving a range of possible scores from 0 (no dysfunction) to 68 (maximum dysfunction).

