### Analysis

We will use intention-to-treat analyses, using multiple imputation to account for missing data and details on the imputation will be reported [74]. Participants will be included in their randomised treatment groups regardless of their post-randomisation behaviour. *P* values less than 0.05 will be considered significant. Outcomes (primary, secondary, and determinants) will be compared between groups as follows: i) *Exercise* vs *Exercise plus weight management*; ii) *Exercise* vs control, and; iii) *Exercise plus weight management* vs control. For continuous data, mean differences in change over time between these groups will be estimated using linear regression models fit to data from both follow-up time points, with random effects for participants, and accounting for clustering by physiotherapist and dietitian in the *Exercise* and *Exercise plus weight management* groups. Models will be adjusted for the stratification variable (history of knee surgery) and values of the outcome at baseline. Terms for time and treatment will be included, with an interaction between the two. Regression assumptions will be assessed using standard diagnostic plots. For binary outcomes, logistic regression models will be fit using generalised estimating equations to account for clustering, with risk differences and 95% confidence intervals calculated. This will include a comparison of the proportion of participants in each group whose improvement meets or exceeds the minimal clinically important difference for each of the primary outcomes. For ordinal outcomes, proportional odds models will be fit similarly. Multinominal models will be applied if the assumption of proportional odds is not valid. To assess the sensitivity of the results for the primary outcomes in situations in which the outcomes are missing not at random, we will apply a pattern-mixture approach that involves fitting regression models that adjust for departures from the missing at random assumption [75].

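### Within each pairwise comparison, benefit may be claimed on pain or function at p<0.05 each with no adjustment stated, so the two-sided error is about 7.8–9.7% instead of 5%

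*Protocol article*

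**What the plan says.** The Abstract (Methods) sets two primary outcomes at one time point: "Primary outcomes are self-reported knee pain and physical function at 6 months". The Primary outcomes section defines them as an 11-point pain rating and the WOMAC function subscale.

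Trial sample size then gives a success rule that joins them: "the intervention will be considered beneficial if it changes either one or both of the primary outcomes". The same section bases the calculation on a "two-sided significance level of 0.05".

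The Analysis section states that *P* "values less than 0.05 will be considered significant" and applies three pairwise comparisons to all outcomes: Exercise against Exercise plus weight management, and each of these against control. The Background hypothesises a difference for all three, including that "both interventions will be more effective than information only".

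The article states no adjustment, hierarchy, gatekeeping or closed-testing rule for the two primary outcomes.

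**The concern.** Two outcomes here serve one claim, that an intervention is beneficial, and either is enough to support it. If each is tested at the full 0.05, the claim has two chances to succeed by accident. The 0.05 used in the sample size is then the error rate of one test and not of the rule the protocol says it will use.

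The protocol itself describes the weight-management programme as costly relative to the exercise components, and the trial is meant to inform future services. A statement that adding the programme is beneficial should carry the error rate the plan appears to promise.

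**Working it through.** **Inputs from the protocol article.** Effect sizes 0.3 (Exercise vs Exercise plus weight management) and 0.4 (least-performing treatment vs control); baseline to follow-up correlation 0.4; power 80%; two-sided alpha 0.05; 15% loss to follow-up; allocation 5:5:2; detectable effect 0.32 after clustering. **Assumed:** the correlation between the pain and function test statistics, taken from 0 to 0.8, with 0.9 as a further check.

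**1. Reproduce the planned sample size.** With baseline adjustment the residual variance is 1 − 0.4² = 0.84, and (1.960 + 0.842)² = 7.849.
- Treatment arms: n = 2 × 7.849 × 0.84 / 0.3² = 146.5, so 147 evaluable; 147 / 0.85 gives 173.
- Control, with 2.5 treated per control: n = 7.849 × 0.84 × (1 + 1/2.5) / 0.4² = 57.7, so 58 evaluable; 58 / 0.85 gives 69.
- Total: 173 + 173 + 69 = 415, as stated.

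The stated numbers are therefore those of one outcome tested at the undivided 0.05.

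**2. Error of the either-or rule within one comparison.** If the two tests were independent, the chance of at least one p<0.05 under the null is 1 − 0.95² = 9.75%. In the favourable direction only, it is 1 − 0.975² = 4.9%. For correlated outcomes, 4 million draws under the null gave:

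| Pain-function correlation | Either direction (nominal 5%) | Favourable only (nominal 2.5%) |
|---|---|---|
| 0 | 9.7% | 4.9% |
| 0.3 | 9.5% | 4.8% |
| 0.5 | 9.1% | 4.5% |
| 0.7 | 8.3% | 4.2% |
| 0.8 | 7.8% | 3.9% |
| 0.9 | 7.0% | 3.5% |

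The figures are the same for each of the three comparisons, to simulation error.

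**3. Error with Hochberg across the two outcomes.** Benefit is claimed if both p<0.05 or the smaller p<0.025. The error per comparison, in either direction, is about 4.4–5.0% (correlation 0.8 to 0).

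**4. Power with Hochberg at an effect of 0.3, before clustering.** With 173 × 0.85 = 147.05 evaluable per treatment arm, the standard error is √(0.84 × 2 / 147.05) = 0.1069 and the expected z is 0.3 / 0.1069 = 2.807.
- One outcome affected, unadjusted: Φ(2.807 − 1.960) = 80%.
- One outcome affected, tested at 0.025: Φ(2.807 − 2.241) = 71.4%. Hochberg adds a little, giving about 72%.
- Both affected, at least one claimed: 92.6%, 86.4%, 83.5% and 81.7% at correlations 0, 0.5, 0.7 and 0.8.

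**5. The same after clustering.** An effect of 0.32 has 80% power under the protocol's clustering, so the expected z at 0.3 is 2.802 × 0.3 / 0.32 = 2.626.
- One outcome affected: Φ(2.626 − 1.960) = 75% unadjusted; Φ(2.626 − 2.241) = 65% at 0.025, and about 65% with Hochberg.
- Both affected: 88.7%, 81.5%, 78.2% and 76.3% at the same four correlations.

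**The case against.** **The article is condensed and an analysis plan may exist.** It nowhere says that p-values will be left unadjusted, and a multiplicity procedure is often placed in the analysis plan. The undivided alpha in the sample size does not prove that none is intended, because Hochberg would leave the sample size unchanged too. That is fair. What remains is that the protocol itself fixes both the either-or rule and the 0.05 threshold, and followed as written these give the wrong error rate. Also, the success rule speaks of an intervention changing an outcome, not of a p-value. Linking it to p<0.05 is an inference, but 0.05 is the only criterion the document offers.

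**Primary outcomes that must both succeed need no adjustment.** True, but the protocol says either.

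**A reader might infer that the error rate is 18–23% over the trial instead of 5%.** That is the chance of at least one significant result over all six primary tests (three comparisons by two outcomes, correlation 0.8 to 0). The arithmetic is right, but it measures a rule the document does not contain. The success rule concerns an intervention across two outcomes. Nothing says the trial succeeds if any comparison is significant, or promises 5% over all three. Statisticians differ on whether distinct questions in a multi-arm trial form one family. Hochberg within each comparison would still leave about 11–12% over the trial, so it is no remedy for that quantity. The figure is context only.

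**A reader might also take 8–10% as the rate of false benefit.** It counts differences in either direction. The favourable-only rate is 3.9–4.9%; the relative inflation is about the same.

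**Conclusion.** The point holds within each pairwise comparison. As written, the rule has a two-sided error of 7.8–9.7%, about 1.6 to 1.9 times the stated 5%. It rests on reading the success rule together with the 0.05 threshold, and on an assumed pain-function correlation of 0.8 to 0. The upper end needs two self-reports on the same knee to be uncorrelated, so the lower part of the range is the more plausible. At 0.9 the error is about 7%, still above 5%.

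No defect is shown across the three comparisons. Severity: should be fixed.

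**What to change.** Keep the either-or rule and state, before the unblinded analysis, that Hochberg (or Holm) is applied to pain and function at 6 months within each pairwise comparison. For Hochberg: claim benefit if both p-values are below 0.05, or if the smaller is below 0.025. If the analysis plan already contains such a rule, the protocol's wording should point to it. Alternatively, drop the either-or claim and report and interpret each outcome separately. It would also help to say whether the three comparisons are regarded as separate questions.

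The change is one paragraph and needs no extra participants. The cost is power at an effect of 0.3:
- Only one outcome affected: from 80% to about 72% before clustering, and from about 75% to 65% after.
- Both affected, at least one claimed: about 82–93% before clustering and 76–89% after (correlation 0.8 to 0). At the higher correlations this is below 80% once clustering is counted.

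Keeping 80% power for each outcome at 0.025, before clustering, would need 178 / 0.85 = 210 per treatment arm and 70 / 0.85 = 83 controls. That is 210 + 210 + 83 = 503 instead of 415, and the fix above does not require it.

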### Analysis

We will use intention-to-treat analyses, using multiple imputation to account for missing data and details on the imputation will be reported [74]. Participants will be included in their randomised treatment groups regardless of their post-randomisation behaviour. *P* values less than 0.05 will be considered significant. Outcomes (primary, secondary, and determinants) will be compared between groups as follows: i) *Exercise* vs *Exercise plus weight management*; ii) *Exercise* vs control, and; iii) *Exercise plus weight management* vs control. For continuous data, mean differences in change over time between these groups will be estimated using linear regression models fit to data from both follow-up time points, with random effects for participants, and accounting for clustering by physiotherapist and dietitian in the *Exercise* and *Exercise plus weight management* groups. Models will be adjusted for the stratification variable (history of knee surgery) and values of the outcome at baseline. Terms for time and treatment will be included, with an interaction between the two. Regression assumptions will be assessed using standard diagnostic plots. For binary outcomes, logistic regression models will be fit using generalised estimating equations to account for clustering, with risk differences and 95% confidence intervals calculated. This will include a comparison of the proportion of participants in each group whose improvement meets or exceeds the minimal clinically important difference for each of the primary outcomes. For ordinal outcomes, proportional odds models will be fit similarly. Multinominal models will be applied if the assumption of proportional odds is not valid. To assess the sensitivity of the results for the primary outcomes in situations in which the outcomes are missing not at random, we will apply a pattern-mixture approach that involves fitting regression models that adjust for departures from the missing at random assumption [75].

Economic evaluations will assess and compare the cost-effectiveness of the interventions. This will involve analysis of: i) cost per extra person with a clinically significant improvement in pain (measured as 1.8 point reduction on the pain score) and function (6 unadjusted WOMAC units), and; ii) per quality-adjusted life years (QALYs) gained for the intervention compared to control at 12 months. QALYs will be calculated based on utility scores using the AQoL-8D at baseline and 12 months. The difference in health care usage and productivity lost between baseline and 12 months will be compared for intervention and control groups. The association between utility gains on the AQoL-8D and productivity will also be compared between the intervention and control groups.

To evaluate the longer-term effects of the *Exercise* and *Exercise plus weight management* interventions on total knee joint replacement and knee arthroscopy surgical rates, logistic regression models for surgery will be fit using generalised estimating equations to account for clustering by physiotherapist and dietitian, with treatment effects summarised using risk differences and 95% confidence intervals. The stratifying variable of history of knee surgery will be adjusted for.

To evaluate whether there is a relationship between amount of weight loss and changes in pain and/or function, linear regression models for changes in pain and outcome will be fit and will include a term for weight lost at 6 and 12 months (as percentage of baseline weight), adjusting for baseline level of the outcome, assigned treatment group, and stratifying variables. Demographic variables thought to affect both weight loss and outcomes levels, including age and sex, will also be included in the model. Fractional polynomial terms for weight lost will be assessed to investigate if the relationship between outcomes and weight loss is non-linear. Standard diagnostic plots will be used to assess regression assumptions. We will also evaluate whether there is a relationship between adherence to exercise and changes in pain and/or function by estimating a complier-average causal effect using a two-stage least squares approach [76].

Finally, we will conduct exploratory analyses to investigate whether the relative effects of each intervention on change in each of the primary outcomes is moderated by: i) expectation of treatment effects; ii) sex; iii) pain self-efficacy; iv) BMI; v) employment situation; vi) history of knee surgery (contralateral total knee joint replacement surgery and/or knee arthroscopic surgery); vii) self-efficacy for eating control, and; viii) depression. These moderators were selected based on previous research and/or theoretical plausibility (Table 5). Models will include terms for treatment, the moderator variables, and an interaction between the two. Fractional polynomials will be included for the continuous moderators [88]. The estimated effects of treatment and 95% confidence intervals will be presented for each moderator, with visual representations included for continuous moderators.

**Table 5 Tab5:** Overview of selected demographic and clinical moderators

Selected moderator variables	Justification		
Expectation of treatment effects	Based on evidence that greater treatment expectations are associated with more favourable outcomes in people with osteoarthritis [77–79]. *Hypothesis*: Participants in the intervention groups who have greater treatment expectations will report greater improvement in primary outcomes than those who have lower treatment expectations (relative to control group).		
Sex	Based on evidence that being male is associated with better outcomes in pain and physical function after supervised strengthening exercises [80] and evidence from a review that being female is associated with greater weight loss intentions [81]. *Hypothesis*: Participants in the intervention groups who are male will report greater improvement in primary outcomes than those who are female (relative to control). Participants in the *Exercise plus weight management* group who are female will report greater improvement in primary outcomes than those who are male (relative to *Exercise* group).		
Pain self-efficacy	Based on evidence that higher self-efficacy associated with better outcomes in pain and quality of life after supervised neuromuscular exercise [82], and greater improvements in pain after and internet-delivered exercise and education program [83]. *Hypothesis*: Participants in the intervention groups who have higher self-efficacy at baseline will report greater improvement in primary outcomes than those who have lower self-efficacy (relative to control group).		
Body mass index	Based on evidence that obesity is associated with better outcomes in quality of life after supervised aquatic exercise [84] and evidence from a review that higher initial BMI is associated with greater weight loss [85]. *Hypothesis*: Participants in the intervention groups who have a higher BMI will report greater improvement in primary outcomes (relative to control) than those who have a lower BMI. Participants in the *Exercise plus weight management* group who have a higher BMI will report greater improvement in primary outcomes than those with a lower BMI (relative to *Exercise* group).		
Employment situation	Based on evidence that being employed associated with greater improvements in pain after an internet-delivered exercise and education program [83]. *Hypothesis*: Participants in the intervention groups who are employed will report greater improvement in primary outcomes than those who are not employed (relative to control group).		
History of knee surgery	Chosen based on theoretical plausibility that knee surgical experience could affect expectations of outcomes and motivation *Hypothesis*: Participants in the intervention groups who have a history of knee surgery will report less improvement in primary outcomes than those without (relative to control group).		
Self-efficacy for eating control	Based on evidence from a review that better control of over-eating and dietary restraint is associated with weight loss and maintenance [86, 87]. *Hypothesis*: Participants in the *Exercise plus weight management* group who have higher self-efficacy for eating control will report greater improvement in primary outcomes than those with lower self-efficacy for eating control (relative to *Exercise* group and to control group).		
Depression	Based on evidence that fewer depressive symptoms is associated with better outcomes in pain and physical function after supervised strengthening exercises [80]. *Hypothesis*: Participants in the intervention groups who have more depressive symptoms at baseline will report less improvement in primary outcomes than those who have less depressive symptoms (relative to control group).		

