### Randomisation allocation concealment and blinding

The randomisation schedule is computer generated and prepared by the study biostatistician. Following completion of the baseline questionnaire, participants are randomly allocated to either the *Exercise* group, the *Exercise plus weight management* group, or the information only (*Control*) group. Due to the differences expected to be observed between treatment groups (effect size of 0.3) and between the least-performing treatment group and the control group (effect size of 0.4), to minimise the number of control group participants required, we will recruit fewer participants in the control group than in either treatment group: see details in the Trial sample size section below. This leads to a randomisation ratio of 5:5:2 (for every 5 participants randomised to a treatment group, we will only randomise 2 to the control group). We expect to see a smaller difference between the two treatment groups than between the least-performing treatment group and the control group. Randomisation will be stratified by history of knee surgery (arthroscopy or contralateral arthroplasty). Participants allocated to the *Exercise* group are randomly allocated to one of three physiotherapists. Participants allocated to the *Exercise plus weight management* group are randomly allocated to one of the same three physiotherapists as in the *Exercise* group, and one of five dietitians. If a physiotherapist or dietitian is unavailable (e.g. sick, on holidays), participants are re-randomised to another available clinician. To conceal group allocation, a researcher not involved in participant recruitment accesses the randomisation schedule via a password-protected computer program.

Given that all primary and secondary outcomes are self-reported, participants are also the assessors. Participants are blinded to study hypotheses, however the components of each treatment arm are disclosed during recruitment. This replicates real-world conditions whereby consumers are fully informed about the nature of the treatment components before choosing whether or not to participate/receive an intervention. Physiotherapists and dietitians are not blinded to group allocation.

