### Physiotherapist and dietitian training

Three musculoskeletal physiotherapists are employed to deliver the intervention. Physiotherapist selection criteria includes having experience managing people with chronic diseases, specifically knee OA, and current registration with the Australian Health Practitioner Regulation Agency. Five accredited dietitians, with at least 2 years of clinical experience and some experience assisting people with weight loss, are employed to deliver the weight management intervention. Prior to the start of the trial, clinicians complete training in:
i)best-practice OA management: dietitians attend a half day workshop in evidence-based management of OA, delivered by members of the research team. Briefly, this includes an introduction to the purpose of the trial, OA definition, diagnosis, risk factors and prognosis, evidence-based practice (including education, exercise therapy, weight loss, and psychological treatments), and principles of shared decision-making and health behaviour change techniques.ii)motivational interviewing skills: dietitians and physiotherapists attend a 2-day training course from Health & Wellbeing Training Consultants, who specialise in training clinicians in motivational interviewing. Case studies presented during trained are designed to replicate potential scenarios anticipated to arise during the trial. Following these first two training days, clinicians conduct an initial and follow-up video consultation with a practice participant (one per clinician) to practice using their motivational interviewing skills and recording consultation notes. Practice consultations are audio recorded and audited for fidelity by a member of the research team using the Motivational Interviewing Treatment Integrity tool (MITI 4.2.1). Group level feedback is provided to clinicians at a half day workshop approximately 1 month after the initial two training days;iii)VLCD: dietitians attend a 1-h webinar delivered by the research team on the specifics of the VLCD. Physiotherapists are asked to watch the video recording of the presentation.iv)study-specific protocols: dietitians and physiotherapists attend a 1–2 h session (supplemented by detailed study treatment manuals) to ensure clinicians were familiar with all study procedures and processes. All clinicians are provided with a hardcopy of the study manual as well as hardcopies of all participant booklets to aid discussions during consultations.

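### GEE for the binary and ordinal outcomes would rest on three physiotherapists and five dietitians, too few clusters for the standard robust test, which rejects a true null in about 9–14% of trials instead of 5%

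*Protocol article*

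**What the plan says.** The Analysis section of the protocol article sets one method for all binary outcomes: "logistic regression models will be fit using generalised estimating equations to account for clustering, with risk differences and 95% confidence intervals calculated". It applies this to the proportion in each group whose improvement reaches the minimal clinically important difference on each primary outcome. It then adds: "For ordinal outcomes, proportional odds models will be fit similarly". Later in the same section, the long-term surgery models are fitted "using generalised estimating equations to account for clustering by physiotherapist and dietitian".

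The number of clusters is given elsewhere. The section on clinician training says: "Three musculoskeletal physiotherapists are employed to deliver the intervention". The randomisation section allocates the combined arm to "one of the same three physiotherapists as in the" Exercise arm, and also to "one of five dietitians". The Trial sample size section says that the control arm has no clustering, and expects an intra-cluster correlation (ICC) of the order of 0.01.

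The first comparison listed is Exercise vs Exercise plus weight management, judged at P < 0.05.

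**The concern.** The robust variance in GEE is justified as the number of independent clusters grows. The number of participants does not help. With three and five clusters, the variance is estimated from a handful of cluster totals of residuals, and these are forced to sum to zero within each arm. Two errors follow. The variance is biased downward, and it is so imprecise that a normal critical value is too small.

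The structure is also awkward for GEE. In the combined arm each participant belongs to a physiotherapist and to a dietitian, the same physiotherapists serve both active arms, and most outcomes are measured at both 6 and 12 months. One ordinary cluster index does not describe this, and the article does not say how the two clinician types enter.

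The results at stake are the responder comparisons for pain and function, appointments with a surgeon, knee surgery, global change, satisfaction, willingness to undergo surgery, and the 2- and 5-year surgery rates. Intervals that are too narrow could make the costlier arm appear to differ from exercise alone when it does not.

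**Working it through.** **1. The plan's own figures.** Inputs from Trial sample size: effect sizes 0.3 and 0.4, baseline–follow-up correlation 0.4, power 80%, two-sided 0.05, 15% loss, five dietitians, ICC 0.01. The 5:5:2 allocation is from the randomisation section.

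- Active arms: 2 × (1.96 + 0.842)² × (1 − 0.4²) / 0.3² = 146.5, so 147. Then 147 / 0.85 = 172.9, so 173.
- Control (ratio 2.5 to 1): (1.96 + 0.842)² × 0.84 × (1 + 1/2.5) / 0.4² = 57.7, so 58. Then 58 / 0.85 = 68.2, so 69.
- Total: 173 + 173 + 69 = 415, as stated.
- Detectable effect: the design effect in the dietitian arm is 1 + (147/5 − 1) × 0.01 = 1.284. Then 2.802 × √0.84 × √((1 + 1.284)/147) = 0.320, as stated.

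These reproduce. After 15% loss there are about 147, 147 and 59 participants for analysis. The article states no error rate for the GEE analyses.

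**2. Rough theory, ICC 0, equal cluster sizes.** With k clusters in an arm, the uncorrected robust variance is on average (k − 1)/k of its true value.

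- Physiotherapist only (k = 3): the factor is 2/3 on 2 degrees of freedom. P(|t₂| > 1.96 × √(2/3)) = P(|t₂| > 1.60) = 25%.
- Physiotherapist in the Exercise arm, dietitian in the combined arm (3 + 5): the mean factor is (2/3 + 4/5)/2 = 0.733, with 2 + 4 = 6 degrees of freedom. P(|t₆| > 1.96 × √0.733) = P(|t₆| > 1.68) = 14%.

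**3. Simulation of a true null at ICC 0.01.** Exercise vs Exercise plus weight management, 147 per arm, nominal two-sided 5%, uncorrected robust variance, normal reference. The first results column is a closed-form risk difference (20,000 runs at each of three event rates: 0.05, 0.3 and 0.5). The second is fitted logistic GEE with 59 singleton controls, adjusted for surgery history (600 runs per setting, independence and exchangeable working correlation).

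| Cluster definition | Risk difference | Fitted GEE |
|---|---|---|
| 3 physiotherapists + 5 dietitians | 12.5–14.0% | 13.8–14.2% |
| 3 physiotherapists + 15 physiotherapist-by-dietitian cells | 10.0–11.0% | 10.2–12.5% |
| 3 physiotherapists only | 25.5–27.1% | 24.8–25.8% |
| Clinicians ignored | 5.1–6.7% | not run |

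Further runs with both clinician types in the definition went as low as about 9%, so the overall range is about 9–14%. A two-way crossed robust variance rejected in about 19% of runs and was not positive in about 13%.

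**4. Source of the inflation.** With ICC set to 0, the closed-form rates are still 11–15% with both clinician types and 25–26% with physiotherapist only. The cause is the number of clusters, so a small true ICC does not protect the analysis.

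**5. With a correction, ICC 0.01.** For 3 + 5 clusters, scale the arm variances by 3/2 and 5/4 and use the t critical value on 6 degrees of freedom (2.447). The error is then 4.3–5.2%. A bias-reduced variance with a normal reference gave 5.2% (3 + 5) and 5.5% (3 + 15) in the fitted GEE runs, but 14.5% with physiotherapist only. That correction does not rescue a three-cluster definition.

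**The case against.** The strongest reply is that the article never writes "sandwich" or "normal reference", gives no working correlation, and does not define the cluster variable for most outcomes. Such details usually sit in a statistical analysis plan, which is not shown and could specify a correction. With one, the error rate is close to 5% unless clusters are defined by physiotherapist alone. This stands in part: GEE as such is not the error, and the figures describe its standard form. But the article does fix a method that relies on many clusters and applies it to three and five.

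Three stronger readings are tempting and are not supported.

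- A reader might infer error rates near 30%. Rates of that order need clustering on physiotherapist alone. The surgery models name "generalised estimating equations to account for clustering by physiotherapist and dietitian", and the sample size section describes both in the combined arm.
- A reader might infer that the main conclusion is unsafe. The primary outcomes are continuous and are analysed by linear models with random effects for participants. For Exercise vs control, where controls are unclustered, simulated inflation was only 7–8% even with physiotherapist clusters.
- A reader might infer that GEE cannot represent crossed clinicians at all. A two-way crossed variance exists; it simply performs badly here.

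It is also fair to object that mixed logistic models are no proven cure. The article states no method for clinician effects even in the continuous models, and only a linear mixed model was checked (5.5% at ICC 0.01).

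**Conclusion.** The concern holds as a should-fix for the binary and ordinal analyses. Followed in its standard form, the planned GEE test of the two active arms has a type I error of about 9–14% at the protocol's ICC of 0.01 when both clinician types define the clusters, and about 25–27% if only physiotherapist does. Leaving clinicians out gives about 5–6% (6.7% at the highest event rate tried). At the protocol's own ICC, the uncorrected adjustment is therefore worse than none.

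This rests on an uncorrected robust variance with a normal reference, 147 participants per active arm, and assumed event rates of 0.05 to 0.5. The ordinal models were not simulated; they are included because the same dependence on the number of clusters applies.

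**What to change.** State the cluster definition for all GEE analyses: physiotherapist in the Exercise arm, dietitian or physiotherapist-by-dietitian cell in the combined arm, each control participant as a singleton, and repeated measures nested within cluster. Do not cluster on physiotherapist alone. Specify a small-sample-corrected variance with a t reference, about 6 degrees of freedom for 3 + 5 clusters, and apply it to the risk differences and their intervals and to the ordinal models.

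A mixed logistic or cumulative-logit model with clinician random intercepts and standardised risk differences can serve as an alternative or sensitivity analysis, once its error rate has been checked by simulation with three and five clinicians. It may fail to converge for rare outcomes such as surgery.

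The cost is a few lines of analysis-plan text, a little more programming and somewhat wider intervals. Sample size and data collection do not change.
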